### Settings and Sampling

The target population is adults diagnosed with BD who are under treatment. The recruitment will be implemented in collaboration with the mental health services used by the participants. Specifically, both private and public mental health services in Cyprus have been informed about the objectives and procedures of the study through a specific communication process. Through this process, several patients have already been referred to the research team by their psychiatrists/therapeutic team coordinator to participate in Stage 1. As a result, convenience sampling will be combined with snowball sampling, according to study inclusion criteria set in every stage. The study is also posted on social media and groups related to BD (health care service users, health care professionals).

To promote participant retention, an action plan has been developed. Specifically, the principal investigator (AH) will arrange one or two social meetings with the participants of Stage 1 and Stage 3 to achieve some degree of intimacy, emphasize confidentiality, and ensure engagement with the study. The cost of these social meetings is covered by the Nursing Department of Cyprus University of Technology. Regarding the control group of Stage 3, the principal investigator (AH) will also make a phone call once or twice per month to reassure their participation in the study, as follows: “Hello, I am [name] from the MoB project. I’m calling to see how you are, and if you are still interested in participating in the project. The next appointment will be on date X. Is this okay with you, or do you have any other arrangements for the day?”

### Stage 1

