#### Inclusion and Exclusion Criteria

The following inclusion criteria have been set for participation in the MoB intervention: (1) clinical diagnosis based on the Diagnostic and Statistical Manual of Mental Disorders-5 for BD; (2) aged between 18 and 65 years; (3) signed the informed consent form; (4) stable mood status at the beginning of the MoB in-person intervention based on clinical assessment, conducted by the principal investigator (AH); (5) experience of the illness for at least 1 year based on the medical record; (6) adequate awareness of the illness, based on the following guide: (a) are you aware of the reason(s) you are using mental health services/under medication? and (b) are you aware of the aim of the educational intervention in which you may participate?; and (7) familiarity with computer use.

The exclusion criteria are: (1) intellectual disability (IQ<70), based on the Wechsler Adult Intelligence Scale [42]; (2) brain damage (eg, following a stroke) based on diagnostic tests; (3) acute phase of the illness, based on clinical assessment and use of the Young Mania Rating Scale (YMRS; total score <12) [43] and/or Beck Depression Inventory (total score <17) [44]; and (4) substance use problems at the beginning of this stage according to the Alcohol Use Disorders Identification Test (AUDIT; total score <9) [45] and Drug Use Disorders Identification Test (DUDIT; total score <2 for women or <6 for men) [46].

All eligible participants will be randomly assigned (in terms of gender, age, duration of illness) into the intervention group and the control (waiting) group. With the aim of obtaining a moderate correlation effect, with 80% statistical power and .05 level of statistical significance, 40 participants are needed in the intervention group and 40 participants are needed in the control (waiting) group.

The criteria for discontinuing participation in the intervention group are disorder relapse and nonadherence to pharmacotherapy (discontinuation of medication).

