#### Effectiveness Evaluation

Evaluation of the effectiveness of the MoB in-person intervention will be based on the degree of improvement in the following outcome variables defined according to the findings of the literature review completed in Stage 1: (1) self-perceived quality of life level, as measured by the World Health Organization Quality of Life Assessment (WHOQOL) tool [47]; (2) self-perceived health-related locus of control, as measured by the Multidimensional Health Locus of Control (MHLC) scale [48]; (3) ability to control impulses, as reflected in one’s sexual and aggressive behavior, measured by the items “aggressive behavior” and “sexual interest” of the YMRS [43]; (4) substance use problems, measured by the AUDIT (alcohol use) [45] and DUDIT (drug use) [46] tools; (5) adherence to pharmacotherapy, measured by the Drug Attitude Inventory (DAI-30) tool [49]; (6) frequency of relapses assessed by the reduction of the number and duration of hospitalizations for the 2 years following the end of the educational intervention; and (7) BD knowledge level assessed by the Bipolar Disorder Knowledge Scale (BDKS) [50].

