The degree of self-perceived quality of life will be measured by the total score in the WHOQOL scale assessment. This is a 1-5 Likert-type scale including 26 items. The minimum score in the scale is 26 and the maximum is 130; higher scores indicate a better outcome. The BD level of knowledge will be measured by the total score in the BDKS. This is a 25-item, true-false scale. The items address diagnosis, etiology, disease course, symptoms, treatment, and life impact BD-related knowledge. The ratio of “true” to “false” responses is assessed; a higher percentage of correct values indicates a better outcome. The degree of ability to control impulses will be measured by the total score in the YMRS. This is a 0-4 Likert scale, including 11 items. The total score of the scale ranges from 0 to 44; a lower total score indicates a better outcome. The degree of adherence to pharmacotherapy will be measured by the total score in the DAI-30. This is a 30-item true-false scale. The ratio of “true” to “false” responses is assessed; a higher percentage of correct values indicates a better outcome. Drug use will be measured by the total score in the DUDIT scale. This is a 1-5 Likert, 11-item scale (total score range: 1-55); a lower total score indicates a better outcome. Alcohol use will be measured by the total score in the AUDIT. This is a 0-4 Likert, 10-item scale (total score range: 0-40); lower scores indicate a better outcome. The degree of self-perceived health-related locus of control will be assessed by the MHLC tool, which is a 6-point Likert (scored from 1 to 6), 18-item scale (Form A). These items are grouped in three subscales corresponding to three different loci of control (ie, internal, others, and fate/luck); higher sum scores in each of the 3 subscales indicate a stronger locus of control. The frequency of relapses will be measured by the number of hospitalizations after completion of the in-person intervention. The number of hospitalizations will be measured as the sum of individual hospitalizations in a high-security psychiatric hospital/setting; the lower the number of hospitalizations, the better the outcome. The duration of relapses will be assessed by the duration of inpatient hospitalizations in days after completion of the in-person intervention. The duration of inpatient hospitalizations will be measured as the sum of the days of hospitalization in a high-security psychiatric hospital/setting; the lower the duration in days of hospitalization, the better the outcome.

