Approximately 5.7 million adults in the United States are diagnosed with BD annually, a percentage corresponding to 2.6% of the total adult population [70,71], while BD is the second most prevalent neurobiological (mental) disorder in the Republic of Cyprus, following psychotic thought disorder [71]. The median age of onset for BD is 25 years, although the illness can start in early childhood or late adulthood, having a long-term impact on one’s life [72]. An equal number of men and women develop BD, and this condition is found in all ethnic groups and social classes [72]. Most importantly, BD results in a 9.2-year reduction in expected lifespan, and as many as 1 in 5 individuals with BD attempts suicide [72]. Additionally, a prolonged lack of diagnosis or false diagnosis at some point of the illness trajectory is a common phenomenon among people with BD [73]. As a result of delayed effective treatment, the symptoms of the disorder become more severe, along with an increased frequency of relapse [74,75]. All of the above constitute the application of innovative, multidimensional, and effective therapeutic approaches aiming to increase the quality of life of this clinical group and adequately empower patients as an imperative goal. Empowerment in the context of health care refers to the status in which service users may function under the highest degree of autonomy, achieve their personal life goals, and gain the optimum level of quality of life [76,77]. Studies on the effectiveness of therapeutic methods aiming to empower ill health self-management skills in people with chronic illness, including BD, have been reported to be necessary [78,79].

Several changes have been made to mental health services in Cyprus; today, the majority of services are provided in community rather than institutional settings. According to the goals of the Ministry of Health of the Republic of Cyprus, advanced, evidence-based mental health clinical practices are considered an integral part of the therapeutic interprofessional approach toward clinical populations [71]. However, to our knowledge, there is no evidence of the extent to which empowering-oriented approaches toward individuals diagnosed with BD have been incorporated to the recent modification of mental health services. Implementation of the proposed intervention is expected to contribute to this goal in Cyprus.

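### The relapse outcome counts only stays in a high-security psychiatric setting, and depression is not measured after entry, so it captures only the severest relapses and a null result would be hard to interpret

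*Protocol article*

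**What the plan says.** Relapse is one of seven outcomes listed under Effectiveness Evaluation, Stage 3. The list gives it as "frequency of relapses assessed by the reduction of the number and duration of hospitalizations for the 2 years following the end of the educational intervention", with no restriction on the type of hospital.

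The scoring paragraph in the same section begins equally broadly: "The frequency of relapses will be measured by the number of hospitalizations after completion of the in-person intervention". It then narrows the count: "The number of hospitalizations will be measured as the sum of individual hospitalizations in a high-security psychiatric hospital/setting". Duration is restricted in the same way, to the "sum of the days of hospitalization in a high-security psychiatric hospital/setting". No other relapse measure is given.

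Two statements elsewhere bear on this. Settings and Sampling says that "both private and public mental health services in Cyprus have been informed" about the study. Projected Findings and Significance says of present-day Cyprus that "the majority of services are provided in community rather than institutional settings".

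Depressive symptoms are scored once, in the Inclusion and Exclusion Criteria, as "Beck Depression Inventory (total score <17". No depression scale appears among the outcomes or in the list of scores under Data Analysis. The Young Mania Rating Scale (YMRS) is repeated, but as a measure of impulse control.

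**The concern.** The listed outcome and its scoring rule do not define the same events. The list covers hospitalizations; the rule covers one kind of hospitalization, and no reason is given for the restriction. A patient who relapses and is admitted to a private clinic or an ordinary psychiatric ward, or who is treated in the community, is recorded as having no relapse.

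Relapse frequency is named in the Aim, and relapse rate is one of two examples in the null hypothesis in the Introduction. If the intervention mainly prevents or shortens episodes that do not end in a high-security stay, the outcome cannot register that benefit. A finding of no difference could mean that the intervention does not work, or that the events it changed were not counted.

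The gap is wider for depression. The trial treats a depressive state as part of the acute phase at entry, then does not score it again.

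**Working it through.** **1. Which events count.** Setting the two relapse statements beside the care setting gives:

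| Event after the in-person intervention | Outcome list | Scoring paragraph |
|---|---|---|
| Stay in a high-security psychiatric setting | counts | counts |
| Admission to any other psychiatric ward, public or private | counts | zero |
| Relapse treated outside hospital | zero | zero |
| Depressive recurrence without a qualifying admission | zero | zero, and no symptom score records it |

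The second row is the contradiction. The third and fourth rows are limits of any admission-based measure. They matter more here because the protocol describes care as mostly community-based.

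**2. What reduction refers to.** The list speaks of "frequency of relapses assessed by the reduction of the number and duration of hospitalizations". The scoring paragraph counts only events after the sessions end, and no count for a period before the intervention is described. Reduction may mean fewer admissions than in the control arm, or a change from an earlier period. The text does not say which.

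**3. Two uses of relapse.** The Inclusion and Exclusion Criteria also make relapse of the disorder a reason to discontinue participation in the intervention group, without defining it. A participant could be discontinued for relapse and still score zero on the relapse outcome.

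**4. Illustration of the cost.** The protocol gives no relapse rate, no admission rate and no share of relapses that reach high security, so there is no figure to reproduce. From the protocol: n = 40 per arm and a .05 significance level, taken here as two-sided. Assumed: relapse proportions p1 (control) and p2 (intervention), and a capture fraction c that is the same in both arms. With a = c·p1, b = c·p2 and m = (a + b)/2,

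power = Φ{[(a − b) − 1.96·√(2m(1 − m)/n)] / √[(a(1 − a) + b(1 − b))/n]}

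Worked case with p1 = 0.40, p2 = 0.20, c = 1: m = 0.30; √(2 × 0.30 × 0.70/40) = 0.1025; 1.96 × 0.1025 = 0.2008; √((0.24 + 0.16)/40) = 0.100; power = Φ((0.200 − 0.2008)/0.100) = Φ(−0.008) = 0.497.

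| Assumed relapse | c = 1 | 0.75 | 0.50 | 0.25 | 0.10 |
|---|---|---|---|---|---|
| 60% vs 30% | 78% | 57% | 36% | 18% | 9% |
| 50% vs 25% | 64% | 46% | 30% | 16% | 8.5% |
| 40% vs 20% | 50% | 36% | 24% | 13% | 7.5% |

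In the 50% vs 25% row, expected participants with an event are 20 vs 10 at full capture (40 × 0.50 and 40 × 0.25) and 5 vs 2.5 at a quarter.

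**5. Sensitivity to the test.** Data Analysis treats relapse frequency and duration as numeric scores compared by t test or analysis of variance, not as proportions. Simulating a t test on assumed Poisson counts with means 0.4/0.2, 0.2/0.1 and 0.1/0.05 gives about 36%, 20% and 13%. Fisher's exact test on 40% vs 20%, 20% vs 10% and 10% vs 5% gives 41%, 16% and 4%. The 4% partly reflects that test's conservatism at small counts: its actual size at 10% vs 10% is about 1.7%. All three methods agree on the direction and disagree on the size.

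**The case against.** The strongest reply is that hospitalization is an accepted, objective marker of relapse. The protocol says that its outcomes follow from its literature review, which reported reduced frequency and length of hospitalization. A restriction to severe stays is then a choice, and the arms can still be compared on it. Depressive symptoms are not a stated objective, and a depressive relapse that leads to a qualifying admission is counted. This stands in part: the outcome is narrow, not void. It does not explain why the list and the scoring paragraph differ, or why the narrower rule was chosen.

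Several stronger readings are tempting, and the protocol does not support them:

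- A reader might infer that most relapses go uncounted. The statement on community care describes services in general; it is not a rate of admission after bipolar relapse.
- A reader might infer that the relapse objective cannot be answered. It is answered, for high-security admissions only.
- A reader might take relapse to be the outcome of the null hypothesis. It is one of two examples there and one of seven outcomes.
- A reader might infer that no reduction can be computed. A between-arm difference is a legitimate reading and needs no earlier count.
- A reader might quote power of 4% as the cost. That rests on assumed rates and on a dichotomised test that the plan does not use.

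The sponsor may also have used the term high-security loosely, for any inpatient psychiatric unit. If so, the text should say so, and the contradiction disappears. Community-treated relapse and depressive recurrence would still be missed.

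**Conclusion.** The point holds in a limited form. Two statements in one section define the relapse outcome differently, and the operative one counts only the severest events. Relapses admitted elsewhere or treated outside hospital score zero, and depressive recurrence without a qualifying admission leaves no trace in the planned data. A null result on relapse would therefore be hard to interpret.

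The size is unknown, because the protocol does not give the share of relapses that reach a high-security setting. Under the assumed rates, halving the capture roughly halves the power at 40 per arm; this shows direction and order of magnitude only. Even full capture gives between 50% and 78% in the normal-approximation scenarios above, so a better definition would improve sensitivity without making relapse a well-powered outcome.

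**What to change.** 1. **Reconcile the two definitions.** In the scoring paragraph, count any psychiatric hospitalization, public or private, for both number and days. Report high-security stays as a subset.
2. **Address depression.** Either repeat the Beck Depression Inventory with the YMRS at the planned evaluations in both arms, as a supportive symptom outcome, or limit the stated relapse objective to admissions.
3. **Say what reduction means.** State whether it is a between-arm difference or a change from a period before the intervention. If the latter, take prior admissions from the medical record, which is already consulted to confirm at least one year of illness.
4. **Do not build a score-based relapse definition yet.** The mood-scale cutoffs are printed with a less-than sign under exclusion criteria, so their direction is unclear, and the relapse that leads to discontinuation is undefined. Both must first be reconciled with the outcome definition.

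The cost is small: changed wording, one more short questionnaire per visit and, if a change score is wanted, one more item from the record. The downside is that admissions outside high-security settings need participant report or a query to the treating service, and are less severe on average. The subset report keeps the severe events visible.

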**Objective:**

This protocol describes the study “Management of my Bipolarity” (MoB), which aims to develop an educational intervention for adults with bipolar disorder and assess its effectiveness. The objectives include (a) a literature review on bipolar disorder educational interventions; (b) a qualitative exploration of the educational needs of people with bipolar disorder; (c) development of an educational intervention based on objectives (a) and (b) (ie, the MoB educational intervention); and (d) exploration of the effectiveness of the intervention regarding participants’ knowledge of their mental health condition and enhancement of their ill health self-management skills. The MoB educational intervention will consist of an in-person and a web-based intervention in the form of a digital platform.

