The proposed protocol focuses on a study aiming to develop an educational intervention for patients with BD, and explores the null hypothesis that patients who solely receive pharmacotherapy will show the same improvement in important aspects of their lives, such as relapse rate and quality of life, compared to those who receive pharmacotherapy and structured educational interventions. The effectiveness of the proposed intervention will be tested in relation to improvement with respect to (a) impulse control, (b) substance use attitudes, (c) adherence to pharmacotherapy, (d) relapse prevention, (e) BD knowledge level, and (f) self-perceived quality of life and locus of health-related control. Thus, the findings of the proposed study are expected to provide data on the effectiveness of a structured educational intervention, which combines in-person and digital interventions, regarding enhancement of ill health self-management skills.

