#### Intervention Procedure

The form of this intervention will be in groups or in person according to the participant’s choice (similar to the data collection process as detailed above). Additionally, all participants of this group will have access to the MoB digital platform and will be assessed via a checklist on the frequency and extent to which they use the digital platform in each in-person session.

The implementation methodology of the MoB in-person intervention will include videos and PowerPoint presentations, as well as interactive learning methods such as role playing, empowerment exercises, and live discussions.

The MoB in-person intervention will comprise a total of 12 educational sessions. Each session will have a duration of 1.5 hours and the maximum number of participants in the groups will be 12 patients. At the beginning of each session, the participants will be given the opportunity to record their feedback for the previous session and the impact of the training intervention so far for themselves and for their families/significant others. The intervention will be performed at Cyprus University of Technology and will be implemented by the principal investigator (AH). Participation in the educational intervention is free of charge. Moreover, there is no financial benefit for those participating in the study (participants, researchers) in terms of reimbursement or any other material benefit.

Those who wish to withdraw participation prior to completion of the intervention will be able to continue to receive information/knowledge about their illness through the digital platform.

The control (waiting) group will only have access to the MoB digital platform. Yet, it should be noted that the control (waiting) group will also receive the MoB in-person intervention if its effectiveness is shown at the end of the study. In this way, all participants will be given the chance to receive the MoB intervention.

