
There will be four evaluation time points. The first evaluation time point will be prior to implementation of the MoB in-person intervention, the second will take place immediately after completion of the MoB in-person intervention, and the third and fourth evaluations will be applied at 6 and 12 months, respectively, after completion of the MoB in-person intervention. These time points have been determined according to the systematic review completed in Stage 1 [14].

The control group will be assessed via the same evaluation tools as the intervention group, and at the same time periods. This will test the null hypothesis that patients who solely receive pharmacotherapy demonstrate the same improvement as the intervention group.

The educational meetings will be held at Cyprus University of Technology in a room specially designed for this purpose that is soundproof, without windows, and chairs placed in a circular arrangement to allow for eye contact, along with small tables on either side to keep notes.

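### The stated null has a pharmacotherapy-only comparator, but controls also receive the MoB digital platform: the trial tests the add-on effect of the in-person sessions, and the null and conclusions should say so

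*Protocol article*

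**What the plan says.** The null appears twice in the protocol article. The last paragraph of the Introduction says that the study "explores the null hypothesis that patients who solely receive pharmacotherapy will show the same improvement in important aspects of their lives", "compared to those who receive pharmacotherapy and structured educational interventions". Effectiveness Evaluation repeats it when describing the control-group assessments: "This will test the null hypothesis that patients who solely receive pharmacotherapy demonstrate the same improvement as the intervention group".

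Intervention Procedure then sets out what each arm gets. Of the intervention group, who attend the 12 in-person sessions: "all participants of this group will have access to the MoB digital platform". Of the controls: "The control (waiting) group will only have access to the MoB digital platform".

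The abstract's Objective makes the platform part of what is being tested: "The MoB educational intervention will consist of an in-person and a web-based intervention in the form of a digital platform". Methods, Aim describes the same two parts. The Introduction says that the findings will "provide data on the effectiveness of a structured educational intervention, which combines in-person and digital interventions", and the Conclusion looks forward to robust evidence on the MoB educational intervention as a whole.

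Other sections are narrower. Design defines Stage 3 as delivering the in-person intervention and evaluating its effectiveness. Effectiveness Evaluation opens with the same target and times all four evaluations from the in-person intervention. Design gives the platform its own assessment in Stage 4.

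**The concern.** A null hypothesis must name the comparison that the data can make. Here the named comparator is pharmacotherapy alone, and neither arm receives that. If the wording stays, rejecting or retaining the null would be reported as a statement about a group that was not studied.

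The larger risk lies with a null result. It would read as MoB doing no better than pharmacotherapy, when it would show only that the sessions added nothing detectable for people who already had access to the platform. A positive result would carry a smaller risk: credit could go to the combined in-person and digital package, although the digital part is common to both arms and its contribution cancels out of the comparison.

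**Working it through.** The point is about which contrast is estimated, so the check is to set the sections side by side.

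**Step 1. Components by arm** (Intervention Procedure; Settings and Sampling for being under treatment)

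| | Pharmacotherapy | Digital platform | In-person sessions |
|---|---|---|---|
| Comparator named in the null | yes | no | no |
| Intervention arm | yes | yes | yes |
| Control arm as described | yes | yes | no |

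The first and third rows differ in the platform column. The word "only" in the control-arm sentence can be read as excluding the in-person sessions, but that does not remove the platform.

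**Step 2. What is estimated.** Let P be the outcome on pharmacotherapy alone, W what platform access adds, and S what the sessions add on top of the platform.

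- Contrast named in the null: (P + W + S) − P = W + S
- Contrast randomised: (P + W + S) − (P + W) = S

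The two agree only if W = 0, that is, if the platform does nothing. The protocol does not assume this, and it presents the platform as a means of enhancing self-management.

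**Step 3. Which statements S can support**

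- Design (Stage 3) and the opening of Effectiveness Evaluation, effectiveness of the in-person intervention: supported.
- Intervention Procedure, offering controls the in-person intervention if it proves effective: supported.
- The null in the Introduction and in Effectiveness Evaluation: not supported, because it needs W + S.
- Combined-package effectiveness in the Introduction and Conclusion: not supported, because it needs W + S.

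**Step 4. Does Stage 4 supply W?** No. It covers applicability, satisfaction and users' knowledge, with no pharmacotherapy-only comparator.

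**Step 5. Can the effect on power be sized?** Inclusion and Exclusion Criteria gives 40 per arm at 80% power and a .05 level for an effect described only as a moderate correlation. Assuming r = 0.3 and a two-sided test:

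- d = 2r/√(1 − r²) = 0.6/√0.91 = 0.629
- n per arm = 2(1.960 + 0.842)²/0.629², which rounds up to 40, so the stated figure is reproduced.

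The article does not say which contrast this effect refers to. If it is S, the platform in the control arm costs no power. If it is W + S and the platform carries a share f of it, the observable effect is 0.629(1 − f). Normal-approximation power at 40 per arm is then 80% for f = 0, 72% for 0.1, 61% for 0.2, 50% for 0.3 and 29% for 0.5. The documents give no value of f, so anything from no loss to a large one is compatible with them.

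**The case against.** The strongest reply is that this is a wording slip and not a design fault. Design and Effectiveness Evaluation already set the in-person intervention as the Stage 3 target, and sessions plus platform against platform is the right comparison for it. That stands, and it is why the remedy changes no arm, allocation or outcome. It does not rescue the null, which is stated twice with a different comparator and is the only hypothesis in the article.

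Four stronger readings are tempting, and the documents do not support them.

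- **The trial is underpowered because controls are treated.** A reader might infer this. It needs an assumed platform share and the assumption that the planned effect was the package effect. The article gives neither.
- **Controls receive the taught content.** The account of the platform in Results, Stage 2 says that its subject units match topics taught in the sessions. But those units are described as still to come, and as places to register one's own symptoms, events and risk factors. The interactive part was under development, with release expected by the second semester of 2022, while recruitment began in the first semester of 2021. The live part does hold an action plan, homework exercises, self-assessment tools and articles, so controls get something, but not the sessions. Low general traffic (visits of almost 2 minutes, a 68% bounce rate) suggests that use may be slight. Those figures describe all visitors, not trial controls, and light use would not turn the arm into pharmacotherapy alone.
- **Control exposure is unmeasured.** The article says that intervention participants "will be assessed via a checklist on the frequency and extent to which they use the digital platform in each in-person session" and describes nothing similar for controls. In a condensed article that silence is not an error.
- **A positive result would be invalid for the package.** If effects add and the platform does no harm, a positive S understates W + S, so the direction would be conservative. The trial would still not have estimated W + S.

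**Conclusion.** The inconsistency is real, and nothing else in the article resolves it. No randomised arm receives pharmacotherapy alone, so the null in the Introduction and in Effectiveness Evaluation is not the hypothesis that the trial tests. The trial can estimate the add-on effect of the in-person sessions given platform access. It cannot estimate the effect of the combined package against pharmacotherapy.

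The correction changes what may be concluded, but not how the trial is run. It touches both statements of the null and the package-level claims in the Introduction and Conclusion. No dilution of effect or loss of power can be put on it from the documents. The conclusion assumes that both arms continue pharmacotherapy, as the target population and the null imply, and that the control arm gets the platform as Intervention Procedure says.

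**What to change.** - In the Introduction and in Effectiveness Evaluation, restate the null as: no difference in improvement between in-person MoB sessions added to platform access and pharmacotherapy, and platform access with pharmacotherapy.
- In the Introduction and Conclusion, limit what Stage 3 is said to show to the add-on effect of the in-person sessions.
- State that a null result will not be reported as MoB failing to outperform pharmacotherapy alone.
- If controls are in fact not meant to have the platform, Intervention Procedure must be reconciled with the null instead. The sponsor has to say which description holds.
- Optional: record platform use in both arms at the four evaluations already scheduled. Login records alone would be incomplete, because the scientific articles lie outside the password-protected area.

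The cost is wording, plus one usage item if the optional step is taken. The price is a narrower claim: evidence for the sessions, not for the whole package.
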